## Abstract

**Background:**

Body mass index (BMI) (kg/m^2^) is used internationally to assess body mass or adiposity. However, BMI does not discriminate body fat content or distribution and may vary among ethnicities. Many women with normal BMI are considered healthy, but may have an unidentified “hidden fat” profile associated with higher metabolic disease risk. If only BMI is used to indicate healthy body size, it may fail to predict underlying risks of diseases of lifestyle among population subgroups with normal BMI and different adiposity levels or distributions. Higher body fat levels are often attributed to excessive dietary intake and/or inadequate physical activity. These environmental influences regulate genes and proteins that alter energy expenditure/storage. Micro ribonucleic acid (miRNAs) can influence these genes and proteins, are sensitive to diet and exercise and may influence the varied metabolic responses observed between individuals. The study aims are to investigate associations between different body fat profiles and metabolic disease risk; dietary and physical activity patterns as predictors of body fat profiles; and whether these risk factors are associated with the expression of microRNAs related to energy expenditure or fat storage in young New Zealand women. Given the rising prevalence of obesity globally, this research will address a unique gap of knowledge in obesity research.

**Methods/Design:**

A cross-sectional design to investigate 675 NZ European, Māori, and Pacific women aged 16–45 years. Women are classified into three main body fat profiles (*n* = 225 per ethnicity; *n* = 75 per body fat profile): 1) normal BMI, normal body fat percentage (BF%); 2) normal BMI, high BF%; 3) high BMI, high BF%. Regional body composition, biomarkers of metabolic disease risk (i.e. fasting insulin, glucose, HbA1c, lipids), inflammation (i.e. IL-6, TNF-alpha, hs-CRP), associations between lifestyle factors (i.e. dietary intake, physical activity, taste perceptions) and microRNA expression will be investigated.

**Discussion:**

This research targets post-menarcheal, premenopausal women, potentially exhibiting lifestyle behaviours resulting in excess body fat affecting metabolic health. These behaviours may be characterised by specific patterns of microRNA expression that will be explored in terms of tailored solutions specific to body fat profile groups and ethnicities.

**Trial registration:**

ACTRN12613000714785

## Background

Obesity has been described as an excess accumulation and storage of fat in the body, typically due to an increase in size and/or number of fat cells. Excess adiposity is generally accepted as an important risk factor for a range of non-communicable diseases; increased fat in the abdominal area compared with fat around the hips poses greater cardiovascular risks and metabolic dysregulation (Huxley et al. 2010; Martinez et al. 2008; Cameron et al. 2009). Yet, there has been no agreement on defining obesity in terms of body fat percentage (BF%) (Oliveros et al. 2014). A wide variety of BF% cut-off points have been used, varying between 20 to 25% for men and 30 to 37% for women (Oliveros et al. 2014). Alternatively, body mass index (BMI) is used worldwide to assess underweight, normal weight, overweight and obesity in adults of both genders (World Health Organisation 2011; Huxley et al. 2010; Gallagher et al. 1996; World Health Organisation 2000). However, BMI does not take into account body fat content or the differential health risks associated with abdominal (central) versus hip (peripheral) fat (Dulloo et al. 2010). There are also concerns regarding the acceptability of BMI as a reference value in varying ethnicities, as overweight and obesity have been defined based on European population data (Deurenberg 2001; World Health Organisation 2011, World Health Organisation 2000). Pacific people, Māori and Asian communities traditionally have larger and smaller body frames, respectively (Swinburn et al. 2004; Huxley et al. 2010; Deurenberg 2001; Rush et al. 2009; Ministry of Health NZ 2009) and subcutaneous fat patterns vary among ethnicities (Deurenberg and Deurenberg-Yap 2003; Okorodudu et al. 2010). Therefore, BMI is unlikely to accurately predict related disease risk profiles among different population subgroups with normal BMI or those that may have different levels of adiposity with a similar BMI (Gallagher et al. 1996; Deurenberg 2001; Ministry of Health NZ 2009).

Adiposity is likely to be overestimated in people with high BMI that have higher lean body mass (e.g. athletes), whilst underestimation is likely in those with lower BMI and less lean body mass (Oliveros et al. 2014; Romero-Corral et al. 2010; Okorodudu et al. 2010). The concept of metabolically obese normal weight individuals has been previously described (Karelis et al. 2004; De Lorenzo et al. 2006), and is associated with increased metabolic dysregulation. This has been referred to as “Normal Weight Obesity” (De Lorenzo et al. 2006) or as will be used in this study, a hidden body fat profile. However, not all individuals with the “hidden fat” profile may be at risk of metabolic disease, and it is unclear from previous studies whether metabolic dysregulation can be explained by high total fat mass, high BF% or high visceral fat (Oliveros et al. 2014).

During the transition from adolescence to adulthood (15–35 years), women experience larger weight gain than men (Jasik and Lustig 2008). Younger women often practice risky eating (e.g. dieting, fast foods) or lifestyle (e.g. physical inactivity) behaviours and work and environmental pressures may lead to altered food habits resulting in higher BF% that may negatively affect their metabolic profiles (Haslam and James 2005; Keskitalo et al. 2008). Furthermore, different taste sensitivities have been shown to influence dietary habits and metabolic health. A higher preference for sweet taste is associated with increased sugary food consumption (Drewnowski et al. 2012), whilst those who are hypersensitive to fatty acids consume less total fat (Stewart et al. 2010). Specific taste perception profiles may therefore lead to increased adiposity and ultimately reduced metabolic and cardiovascular health (Mendoza et al. 2007; Duffey and Popkin 2008). Gene-environment interactions may also increase the susceptibility of overweight individuals to develop hyperlipidemia, hypertension or diabetes (Martinez et al. 2008; Arkadianos et al. 2007). Excess body fat accumulation is mostly the result of a polygenic syndrome interacting with both dietary and physical activity components of lifestyle (Martinez et al. 2008). The signals delivered by food intake and physical activity regulate genes and proteins that alter energy expenditure/storage (Buttriss 2006). Gene/protein responses to food intake and physical activity vary between individuals; however, the cause is unknown (Martinez et al. 2008). MiRNAs are recently discovered molecules that act as “switches” to “turn on” or “turn off” genes and proteins. They are sensitive to diet and exercise (Güller and Russell 2010) and may influence the varied metabolic response seen between individuals (Davidsen et al. 2011). Recently, specific miRNAs have been suggested as biomarkers for metabolic disease (Heneghan et al. 2011). This unique gene-diet-physical activity relationship might impact on the development of hidden or apparent body fat, with different consequences across ethnic groups and thus requires further investigation (Swinburn et al. 2004; Arkadianos et al. 2007; Deurenberg and Deurenberg-Yap 2003; Di Renzo et al. 2007).

This study will be conducted as a cross-sectional comparative designed study. The primary aim of this study is to explore the metabolic risks and predictive factors associated with the hidden and apparent body fat profiles in 16 to 45 year old (post-menarcheal and premenopausal) NZ European, Māori and Pacific women. The primary outcomes are:Investigating the association between body composition profiles and markers of metabolic disease risk, including glucose, lipid and inflammatory marker profiles;Investigating dietary and physical activity patterns as predictive factors associated with body composition profiles;Investigating miRNA expression related to energy expenditure/storage as a predictive factor associated with body composition profiles.

The secondary outcomes are:Investigating associations/interactions between dietary and physical activity patterns and miRNA expression and how this may modulate the odds of having a specific body composition profile;Investigating taste perceptions as a predictive factor associated with the different body composition profiles;Investigating eating behaviour and habits as predictive factors associated with the different body composition profiles;Investigating nutrient intake as a predictive factor associated with the different body composition profiles.

We hypothesise that the “hidden fat” profile is associated with increased metabolic disease risk in NZ European, Māori, and Pacific women aged 16 to 45 years. We further hypothesise that for all women, dietary and physical activity patterns are predictors of a particular body composition profile by modulating miRNAs associated with energy expenditure/storage.

## Methods/Design

### Study design

The Women’s EXPLORE (“EXamining Predictors Linking Obesity Related Elements”) is a cross-sectional study targeting post-menarcheal, premenopausal NZ women to examine predictors of body composition profiles. Three body composition profile groups will be explored, namely:

“Normal Fat” group – normal BMI (<25 kg/m^2^), normal BF% (≥22%,<30%);

“Hidden Fat” profile group – normal BMI (<25 kg/m^2^), high BF% (≥30%);

“Apparent Fat” profile group – high BMI (≥25 kg/m^2^), high BF% (≥30%) (Oliveros et al. 2014; Okorodudu et al. 2010; NHLBI Obesity Education Initiative Expert Panel on the Identification Evaluation and Treatment of Overweight and Obesity in Adults 1998).

### Participants and sample size

Study participants are adult NZ women from three ethnic groups (NZ European, Māori, and Pacific Island). A total sample size of 225 women per ethnic group, consisting of 75 per profile group, will provide 80% power at significance levels of p < 0.05 to detect a medium effect size *f* of 0.25 (G*Power 3.1.2) for comparing the “hidden fat” profile with the other two body composition profiles (“normal fat” and “apparent fat”) regarding metabolic disease risk markers, dietary and physical activity patterns, and miRNA expression levels.

The medium effect size is relevant to all variables, and encompasses a variety of scenarios, as we wish to be able to explore how metabolic profile changes with body composition. For example, if the three groups have equally spaced means (μ - Δ, μ, μ + Δ), the difference in means will be detected with 80% power when Δ = 0.31 x σ, where σ is the within group standard deviation. For cholesterol, where preliminary data suggests σ = 0.98 mmol/L, we have 80% power to detect the difference when Δ = 0.30 mmol/L. Alternately, if two groups have the same mean μ and the third has mean μ + Δ, 80% power is achieved when Δ > 0.53 x σ, or 0.52 mmol/L in the case of cholesterol. A Δ = 0.30 – 0.52 mmol/L is estimated to be associated with a 9 – 15% lower relative risk of coronary heart disease (CHD)-related mortality (Gould et al. 2007). For HDL-C where preliminary data suggests σ = 0.38 mmol/L we have 80% power to detect a difference when Δ = 0.12 – 0.20 mmol/L. Every 0.1 mmol/L increase in HDL-C has been suggested to reduce CHD risk by between 8 – 15% (Gordon et al. 1989; Turner et al. 1998). For TG where preliminary data suggests σ = 0.45 mmol/L we have 80% power to detect a difference when Δ = 0.14 – 0.24 mmol/L. Studies in women showed a 1 mmol/L increase in TG was associated with 37% increase in risk of CVD (after adjustment for HDL-C and other risk factors)(Austin et al. 1998); Δ of 0.14 – 0.24 is thus estimated to be associated with 5.2 – 9% difference in CVD risk.

The power for simple (one variable) logistic regression for the risk of having a “hidden fat” profile among people of normal BMI is equivalent to the power of the independent sample t-test (Vaeth and Skovlund 2004) for comparing the predictor variable mean between the hidden fat and normal fat profiles. With a sample size of 75 per group and equal variance within groups, 80% power is achieved for differences of 0.46 σ. For instance, preliminary data on total energy expenditure assessed using the Recent Physical Activity Questionnaire (RPAQ) estimates the standard deviation at 5.36 METs-h/day; if the true difference means between the body composition groups is 2.47 METs-h/day, the logistic regression coefficient will be significantly non-zero 80% of the time. Clinically, the difference of 2.47 METs-h/day equates to ~684 kJ/day (164 kcal/day)(Besson et al. 2010), which is considered within the target range of recommended energy expended each day in physical activity and/or exercise (Pescatello and American College of Sports Medicine 2014). We will consider logistic regression predictors from the dietary and activity pattern data, and separately for the miRNA measurements.

Based on our pilot study that showed a prevalence of 21% of NZ European women having a “hidden fat” profile, (Kruger et al. 2010b) a sample of ~1140 women will need to be screened (380 per ethnicity) to find ~75 women per profile group; or to explore new profiles. The study design and study procedures are illustrated in Figure 1.

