### Data handling and statistical analysis

Statistical analysis will be performed using IBM SPSS statistics (IBM Corporation, New York, USA). Descriptive statistics will be used to describe the baseline population using mean (standard deviation), median (25, 75 percentile) or frequencies summary statistics. Normality of distribution will be evaluated using the Kolmogorov-Smirnov test and examining normality plots. Non-normally distributed variables will be transformed into approximately normal distributions by logarithmic transformations and again tested for normality. Primary statistical analyses will involve ANOVA tests with post-hoc analysis and Bonferoni adjustments comparing body composition profile groups regarding metabolic disease risk markers and dietary and physical activity patterns and miRNA levels; multiple logistic regression analysis to determine odds ratios of having a “hidden body fat” profile based on dietary and physical activity patterns; and, separately, miRNA expression levels. Principal components analysis will be performed on the miRNA data using the PCP directive in GenStat to identify linear combinations of the miRNAs that account for most of the variation between individuals (Zacharewicz et al. 2014); and Pearson correlations to determine correlation coefficients between dietary and physical activity patterns and miRNA expression profiles. A p-value of <0.05 will be considered significant.

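### The 80% power stated at Δ = 0.31σ for equally spaced means fits neither the omnibus ANOVA (about 93%) nor a hidden-fat contrast with an adjacent group (31–47%)

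*Protocol article*

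**What the plan says.** All of this is in the protocol article.

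- **Participants and sample size, first paragraph.** "A total sample size of 225 women per ethnic group, consisting of 75 per profile group, will provide 80% power". The level is set at 0.05. The effect size f is "of 0.25 (G*Power 3.1.2"), and the purpose is given as "for comparing the “hidden fat” profile with the other two body composition profiles (“normal fat” and “apparent fat"), for metabolic markers, dietary and activity patterns, and miRNA levels.
- **Same section, first example.** The article writes that "if the three groups have equally spaced means (μ - Δ, μ, μ + Δ), the difference in means will be detected with 80% power". The stated size for this is 0.31σ, with σ the SD within groups. For cholesterol (σ = 0.98 mmol/L) this becomes 0.30 mmol/L. It also supplies the lower ends of the HDL-C range (0.12 mmol/L) and the TG range (0.14 mmol/L).
- **Same section, second example.** When two groups share a mean and the third differs, 80% is said to be reached above 0.53σ: cholesterol 0.52, HDL-C 0.20, TG 0.24 mmol/L.
- **Same section, logistic regression paragraph.** For hidden versus normal fat at 75 per group, treated as a two-sample t-test, 80% is reached at 0.46σ.
- **Data handling and statistical analysis.** "Primary statistical analyses will involve ANOVA tests with post-hoc analysis and Bonferoni adjustments comparing body composition profile groups".
- **Background.** The lead hypothesis is that the hidden-fat "profile is associated with increased metabolic disease risk in NZ European, Māori, and Pacific women aged 16 to 45 years".

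**The concern.** The power claim is worded for comparisons that involve hidden fat, but its effect size describes the spread of all three means. With equally spaced means, much of that spread is the 2Δ gap between the two outer groups. If hidden fat is in the middle, it differs from each neighbour by only Δ. If it is at an end, it still differs from one group by only Δ. So at least one hidden-fat contrast is always 0.31σ, and the plan tests such contrasts post hoc with Bonferroni adjustment.

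The stake is interpretation. The section attaches clinical meaning to the lower ends of its ranges (about 9% lower relative risk of CHD mortality for cholesterol, 5.2% difference in CVD risk for TG). A reader told that 0.30 mmol/L was detectable with 80% power could take a non-significant hidden-versus-normal result as evidence against a difference of that size.

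**Working it through.** **Inputs.** From the sample-size section: 75 per profile, so N = 225 in one ethnic group; α = 0.05; f = 0.25; Δ = 0.31σ and 0.53σ; σ = 0.98 (cholesterol), 0.38 (HDL-C) and 0.45 (TG) mmol/L. From the analysis section: ANOVA, then Bonferroni post-hoc tests. Assumed: two-sided pairwise tests, and three adjusted comparisons (two as a variant), since the article gives no number.

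**Step 1: where the two Δ values come from.**
- Equally spaced means: f = (Δ/σ)·√(2/3), so Δ = 0.25·√(3/2)·σ = 0.306σ. This matches the stated 0.31σ and, for cholesterol, 0.306 × 0.98 = 0.30.
- One group different: f = (Δ/σ)·√2/3, so Δ = 0.25·3/√2·σ = 0.530σ. This matches the stated 0.53σ.

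Both are f = 0.25 rewritten.

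**Step 2: does the omnibus test give 80%?** Noncentral F with 2 and 222 df and noncentrality λ = N·f² = 225 × 0.0625 = 14.06. Power is 92.6%, or 93.2% at Δ = 0.31σ exactly (f = 0.253). For 80% at f = 0.25, about 159 women (53 per group) would be enough. At N = 225, 80% corresponds to f = 0.208. The omnibus test at f = 0.25 comes near 80% (79.6%) at α = 0.01, which is not the stated level. The printed 80% does not reproduce.

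**Step 3: does a contrast of size Δ give 80%?** Noncentral t, pooled error df 222, noncentrality 0.31·√(75/2) = 1.90.

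| Level | Power at 0.31σ | Difference for 80% power |
|---|---|---|
| 0.05, unadjusted | 47.2% | 0.459σ |
| 0.05/2 | 36.2% | 0.506σ |
| 0.05/3 | 30.6% | 0.532σ |

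The two outer groups (2Δ = 0.62σ) have 92% with Bonferroni for three.

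**Step 4: simulation of the first example** (200,000 runs, hidden fat in the middle, Bonferroni for three). The ANOVA is significant in 93%, and each hidden-fat contrast in 31%. At least one hidden-fat contrast is significant in 57%. Among significant ANOVAs, 38% show neither hidden-fat contrast.

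**Step 5: comparison with the logistic regression paragraph.** At 0.46σ, 75 per group and unadjusted α = 0.05, power is 80%, so that figure reproduces. Since 0.46σ is needed without adjustment, 0.31σ between two groups of the same size cannot also have 80%.

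**Step 6: the second example.** At 0.53σ a pairwise test with Bonferroni for three has 79.7%. The stated 80% holds there for a pairwise test.

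**The case against.** The strongest defence has four parts.

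- **The first example may be meant as an omnibus statement.** It speaks of the difference in means without naming a pair. Read that way, 80% is cautious, since the true figure is about 93%. This stands as a reading of that one sentence. It does not rescue the section, because the opening sentence ties the 80% to comparing hidden fat with the other two profiles.
- **Readers are not given 0.30 mmol/L alone.** Cholesterol, HDL-C and TG are each given with a lower and an upper Δ, and the upper value is supportable for a Bonferroni pairwise test. This stands, and it confines the error to the lower end.
- **A two-group calculation is already printed.** The 0.46σ figure is correct, but it is written for logistic predictors and is unadjusted. It does not cover the Bonferroni post-hoc tests, and it contradicts 0.31σ rather than supporting it.
- **The 31% is conditional.** It needs a contrast between adjacent groups, three adjusted comparisons and analysis within one ethnic group. The article does not assign profiles to means or count the comparisons. But at least one hidden-fat contrast equals Δ in any arrangement, even the unadjusted test has only 47%, and the power is stated per ethnic group.

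A reader might infer that the 80% is simply omnibus F-test power. The stated inputs do not support that: only f and the two Δ values are omnibus quantities. A reader might also infer that 75 per profile is too few. The documents do not support that either, since the second example holds for a pairwise test.

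**Conclusion.** The statement of 80% power at Δ = 0.31σ is wrong as written. It is too low for the omnibus test (about 93%) and far too high for a hidden-fat contrast of size Δ: 47% unadjusted, 36% with Bonferroni for two, 31% for three. With either adjustment, such a difference would be missed about 64–69% of the time. It also conflicts with the 0.46σ in the same section, and that conflict needs no assumption about multiplicity.

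The shortfall is confined to the equally spaced example and the lower ends derived from it (0.30, 0.12 and 0.14 mmol/L). The sample size, the planned tests and the 0.53σ example are not put in doubt. The figures rest on two-sided tests, 75 analysed women per profile and analysis within one ethnic group.

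Pooling all 675 women, 225 per profile, would give about 81% at 0.31σ with Bonferroni for three. A reader might infer that the pooled contrast must therefore become the headline test. That does not follow: the article sizes the study within each ethnic group and expects consequences to differ between them, whereas the pooled figure assumes one common difference.

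**What to change.** In the sample-size section:

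1. State which test the 80% refers to.
2. Give the omnibus power at f = 0.25, N = 225 and α = 0.05 as about 93%.
3. Remove 0.31σ (cholesterol 0.30, HDL-C 0.12, TG 0.14 mmol/L) as a detectable difference for hidden fat, together with the risk figures attached to those lower ends.
4. State the difference detectable with 80% power for a hidden-fat contrast within one ethnic group, and name the number of adjusted comparisons:
   - three comparisons: about 0.53σ, that is cholesterol 0.53 × 0.98 = 0.52, HDL-C 0.53 × 0.38 = 0.20, TG 0.53 × 0.45 = 0.24 mmol/L;
   - two comparisons: about 0.51σ, that is 0.50, 0.19 and 0.23 mmol/L.

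The cost is a less favourable stated figure. No participants are added and no planned analysis has to change.

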**Figure 1 Fig1:**
[figure not shown]
**Study design and procedures.**

Inclusion criteria for women are:age (16 to 45 years),being post-menarcheal or pre-menopausal (as defined by a continuous regular menstrual cycle for the past one complete year),ethnicity (being of NZ European, Māori, or Pacific ethnicity as defined by self-identification and having at least one parent from the same ethnicity).

Exclusion criteria for women are:pregnancy and lactation,presence of any diagnosed chronic illness particularly affecting metabolic health (e.g. T2DM),presence of dairy allergy as the taste solution is dairy based.

